### Randomization and blinding

2.4

Eligible participants will be randomized in a 1:1 ratio to the intervention or control group using a computer-generated randomization sequence with randomly permuted block sizes of 4 and 6. Randomization will be stratified by baseline LEMS (10–30 vs. 31–45) and AIS grade (C vs. D) to ensure balanced distribution of prognostic factors between groups. The randomization sequence will be generated by an independent statistician and concealed using a secure, web-based randomization system accessible only to unblinded study personnel.

Given the nature of the intervention, complete participant blinding is challenging. However, the sham TMS procedure will employ established protocols designed to minimize perceptible differences from active stimulation. A specialized sham coil that produces similar acoustic artifacts and scalp sensations without delivering effective magnetic stimulation will be used for the control group. Participants will be informed that they may receive either active or sham TMS and will be asked not to discuss their perceived treatment assignment with assessors.

All outcome assessors will be blinded to treatment allocation. Assessors will not be present during treatment sessions and will be instructed to avoid discussing treatment details with participants. At the conclusion of the study, assessor blinding will be evaluated by asking assessors to guess participants' group assignments; successful blinding will be indicated by assignment accuracy no better than chance (50%).

The TMS and tSCS interventions will be delivered by trained, unblinded research therapists who will not be involved in outcome assessments. Intervention therapists and outcome assessors will work independently, with no overlap in roles, to maintain assessor blinding.

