### Regulatory approval

6.1

This study will be conducted in accordance with the Declaration of Helsinki (2013 revision), ICH-GCP guidelines, and Singapore's Human Biomedical Research Act (2015). The protocol, informed consent forms, and participant-facing materials will be submitted to the National Healthcare Group Domain Specific Review Board (NHG DSRB) for approval prior to study commencement at both sites. Recruitment will not begin until full ethical approval is granted. Any protocol amendments will be submitted to the NHG DSRB prior to implementation. The trial will be prospectively registered on ClinicalTrials.gov before enrolment of the first participant.

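### Section 2.4 prints the block sizes and limits the randomisation system to unblinded staff, so allocation is more predictable than it need be; a cheap, low-priority improvement

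*Protocol article*

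**What the plan says.** Protocol article, section 2.4 (Randomization and blinding):

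- Allocation is 1:1 from a "computer-generated randomization sequence with randomly permuted block sizes of 4 and 6". There are four strata: two bands of baseline LEMS by AIS grade C or D. Site is not a stratification factor.
- An independent statistician generates the sequence, which is "concealed using a secure, web-based randomization system accessible only to unblinded study personnel".
- Treatment is "delivered by trained, unblinded research therapists". These therapists are kept apart from outcome assessment. They are the only unblinded staff the article describes, and this is the only separation of roles it states.

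Section 2.1 names two sites; the abstract names one. Section 2.3 plans 60 participants. Section 6.1 says "Recruitment will not begin until full ethical approval is granted", so the blocking details appear in an article written as if no one has yet been entered. The section does not say who screens, who confirms eligibility or who decides when a participant is randomised.

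**The concern.** Concealment has two parts: nobody who enrols should see the list, and nobody who enrols should be able to predict it. An independently generated list in a web system deals with the first. The second depends on who knows past allocations and how the blocks are built. Here the block sizes are public, and the system is open only to people who may know past allocations.

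If such a person also had a say in which waiting candidate is entered next, candidates expected to do well could be entered when the active arm looks likely. Some entry criteria in Table 1 leave room for judgement, such as medical stability and ability to commit to the whole study. Blinded assessment of LEMS would not protect against this, because the selection comes before treatment. The ANCOVA in section 5.2 adjusts for baseline LEMS, AIS grade, neurological level and site, but not for motivation or other prognosis it does not measure.

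**Working it through.** The article gives no predictability figure, so there is none to reproduce.

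**Inputs from the article.** 1:1 allocation, block sizes 4 and 6, four strata (2 × 2), 60 participants, two sites, target difference 2 LEMS points.

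**Assumptions.** Each block size is equally likely. The strata are equal, at 60 / 4 = 15 each; uneven splits were also run. For the own-site case, each allocation falls at either site with probability one half.

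**Step 1: fixed blocks, for reference.** The guesser names the arm with more places left. In a block of 4 the chances of being right are:

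- first place: 1/2
- second place: 2/3
- third place: (1/3)(1) + (2/3)(1/2) = 2/3
- fourth place: 1

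The mean is (0.500 + 0.667 + 0.667 + 1.000) / 4 = 0.708. The share of allocations known for certain is (1/3 + 1) / 4 = 0.333. The same recursion for blocks of 6 gives 0.683 correct and 0.250 certain.

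**Step 2: the plan's mixed blocks.** The guesser knows both sizes and the stratum's full history, and updates by Bayes' rule on which block is running.

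| Knowledge and stratum sizes | Correct | Certain |
|---|---|---|
| Full history, one stratum of 15 (exact) | 67.6% | 5.9% |
| Full history, four strata of 15 (simulated) | 67.5% | 6.0% |
| Full history, strata of 8, 12, 16, 24 (simulated) | 68.2% | 5.9% |
| Full history, strata of 5, 10, 15, 30 (simulated) | 68.0% | 5.7% |
| Own-site history only, four strata of 15 (simulated) | 56.4% | not computed |
| No knowledge of earlier allocations | 50% | 0% |

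The own-site row uses the simple rule of guessing the arm with fewer participants so far at that site. With full history, about 42–44% of allocations can be called with at least 75% certainty. Mixing 4 and 6 thus removes most of the certain calls seen with fixed blocks but little of the average predictability.

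**Step 3: what this could do to the estimate, as a ceiling.** Suppose every entry could be steered, and steerable candidates differ by D points in expected LEMS change. With guessing accuracy g, the active arm receives a share g of the better candidates and the control arm a share 1 − g. The induced difference is g·D − (1 − g)·D = (2g − 1)·D. The documents give no value for D; 1 to 2 points is assumed.

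- Full history: 2 × 0.676 − 1 = 0.352, so 0.35 to 0.70 points.
- Own-site history: 2 × 0.564 − 1 = 0.128, so 0.13 to 0.26 points.

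Against the 2-point target this is at most 0.70 / 2 = 35% with full history and 0.26 / 2 = 13% with own-site history.

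**The case against.** A reader might infer that entry to this trial can be steered. The article does not support that. No section gives unblinded staff control over screening, consent or order of entry. Table 2 places consent and eligibility at screening and randomisation at baseline, and section 2.4 randomises those already found eligible. The access restriction can be read simply as keeping assessors away from allocations. Who enrols and which user roles exist is detail an article may leave to the full protocol, so silence on it is not a fault. All of this stands.

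Three further points also stand:

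- The 68% needs complete stratum history. Therapists are described as unblinded, but not as knowing every allocation across both sites. The two figures would coincide only if there were a single recruiting site, as the abstract suggests.
- The bias figures need every entry to be steerable, suitable candidates waiting in the same stratum, deliberate steering and an assumed D. They are upper bounds.
- The future tense of section 6.1 is not firm evidence of timing. The same section puts registration in the future although the abstract already carries a registration number.

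The objection does not remove what section 2.4 itself fixes: printed block sizes, and a system reserved for staff who may know past allocations. Independent generation and web concealment protect against sight of the list, not against prediction from history.

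**Conclusion.** The point holds as a design weakness that is cheap to remove. As described, the scheme allows about 68% correct guessing to someone with full stratum history and about 56% to someone with own-site history, with about 6% of allocations certain in the full-history case. These figures rest on equally likely block sizes; the full-history figure barely moves with the split across strata. Whether anyone so informed can influence entry is neither stated nor excluded. No bias is established, and 0.35–0.70 points (0.13–0.26 with own-site history) is only a ceiling on an assumed prognostic difference of 1 to 2 points. Priority is optional to low.

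**What to change.** Before recruitment starts:

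1. The independent statistician regenerates the list, with the block sizes held in a restricted document until the trial ends.
2. Section 2.4 is amended so that staff unaware of earlier allocations lock eligibility, baseline LEMS and AIS grade in the web system and then trigger randomisation. The result is released only to the unblinded therapists. Whoever triggers must not be shown the arm, so that their own blinding is kept.

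If enrolment and treatment roles are already separated in practice, saying so in 2.4 and regenerating the list is enough. The cost is a user-role change in the web system, a new list, one paragraph of text and one extra step at each enrolment. No additional participants or staff are needed.

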### Interventions

2.5

#### Transcranial magnetic stimulation protocol

2.5.1

For the intervention group, repetitive TMS (rTMS) will be delivered using a 70 mm figure-of-eight coil connected to a MagStim BiStim^2^ magnetic stimulator (MagStim Ltd, Whitland, UK). The device has been registered with the Health Sciences Authority (HSA), Singapore, under Class B medical device notification (CRM-N) for research purposes only. The stimulation target will be the leg motor area of the primary motor cortex, identified using established anatomical landmarks and confirmed by eliciting motor evoked potentials (MEPs) in lower extremity muscles when possible. For participants in whom MEPs cannot be reliably elicited, the target will be defined anatomically as the vertex (Cz) position, located using the international 10–20 system surface measurement landmarks (i.e., the intersection of nasion-to-inion and pre-auricular point-to-point midlines). No EEG recording is required; the 10–20 system is used solely as a standardized method for scalp localization.

The rTMS protocol will employ intermittent theta burst stimulation (iTBS), which has been shown to induce robust and sustained increases in cortical excitability with relatively brief stimulation durations (Huang et al., 2005). The iTBS protocol consists of bursts of three pulses at 50 Hz, repeated at 5 Hz (200 ms between bursts), delivered in 2-s trains with 8-s inter-train intervals. Each session will deliver 600 pulses total over approximately 190 s. Stimulation intensity will be set at 80% of the active motor threshold (AMT) or 80% of maximum stimulator output if AMT cannot be determined. AMT will be determined with the participant maintaining a slight voluntary contraction of the target lower limb muscle (approximately 10%−20% of maximum voluntary contraction, confirmed by visual EMG feedback), and defined as the minimum TMS intensity required to elicit MEPs of at least 200 μV peak-to-peak amplitude in 5 of 10 consecutive trials. Where reliable voluntary contraction cannot be achieved due to motor impairment, resting motor threshold (RMT) will be substituted, as defined in Section 3.2.

For the control group, sham TMS will be delivered using a specialized sham coil positioned identically to the active coil. The sham coil produces acoustic clicks and induces mild scalp sensations through electrical stimulation of scalp electrodes, mimicking the experience of active TMS without delivering effective magnetic stimulation to cortical tissue.

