**Neurophysiological Measures:** Motor evoked potentials (MEPs) will be recorded from the tibialis anterior and soleus muscles bilaterally in response to single-pulse TMS over the motor cortex. MEP amplitude (peak-to-peak), MEP latency, and cortical silent period duration will be measured to characterize corticospinal excitability and inhibitory function. Additionally, recruitment curves will be constructed by delivering TMS at intensities ranging from 100% to 150% of motor threshold to assess the input-output properties of corticospinal projections (Rossini et al., 2015).

Motor threshold for neurophysiological assessments is defined as the minimum TMS intensity required to elicit MEPs of ≥50 μV peak-to-peak amplitude in at least 5 out of 10 consecutive trials in the target muscle at rest (resting motor threshold, RMT) or during slight voluntary contraction (active motor threshold, AMT).

**Electromyography (EMG):** Surface electromyography (EMG) will be recorded bilaterally from the tibialis anterior, medial gastrocnemius, rectus femoris, and biceps femoris muscles. Bipolar Ag/AgCl surface electrodes will be placed over the muscle belly in accordance with SENIAM guidelines, with an inter-electrode distance of 20 mm (Hermens et al., 2000). A reference electrode will be placed on the ipsilateral fibular head. Signals will be amplified (gain × 1,000), bandpass filtered (20–500 Hz), and sampled at 2,000 Hz. Data will be acquired using the Noraxon Ultium EMG wireless surface EMG system (Noraxon USA Inc., Scottsdale, AZ, USA) and visualized using Noraxon MR-XP 1.07 software. EMG will be recorded during dedicated assessment sessions at baseline, Week 8, Week 16, and Week 20, and not during treatment sessions. Participants will perform three maximum voluntary isometric contractions of each recorded muscle, each held for 5 s with 60-s rest intervals, to allow normalization of EMG amplitude. Continuous lower limb EMG will also be recorded during the 10MWT at comfortable speed to characterize muscle activation timing and recruitment patterns during gait. Instructions and rest intervals will be standardized across all assessment sessions.

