### Subgroup analyses

5.4

Pre-specified subgroup analyses will examine treatment effects according to baseline LEMS (10–30 vs. 31–45), AIS grade (C vs. D), neurological level (cervical vs. thoracic), time since injury (12–36 months vs. >36 months), study site (NUH vs. Alexandra Hospital), and baseline ambulatory status (non-ambulatory vs. ambulatory with assistance). Subgroup analyses will be considered exploratory and interpreted with appropriate caution given the limited sample size for detecting interaction effects. An additional exploratory subgroup analysis will compare treatment effects between participants in whom MEPs are present at baseline vs. those in whom MEPs cannot be reliably elicited. This analysis will explore whether preservation of corticospinal tract conduction is a prerequisite for, or modifier of, treatment response to combined TMS-tSCS.

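### For active-arm participants who cannot hold a voluntary contraction, Section 2.5.1 gives two conflicting iTBS intensity rules; AMT also has two amplitude criteria, and the assessment threshold's muscle state is not fixed

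*Protocol article*

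**What the plan says.** **Treatment intensity (Section 2.5.1).** The main rule and first fallback are in one sentence: "Stimulation intensity will be set at 80% of the active motor threshold (AMT) or 80% of maximum stimulator output if AMT cannot be determined". AMT is measured while the participant holds a slight contraction of the target leg muscle, and the criterion is "MEPs of at least 200 μV peak-to-peak amplitude in 5 of 10 consecutive trials". A second fallback follows: "Where reliable voluntary contraction cannot be achieved due to motor impairment, resting motor threshold (RMT) will be substituted, as defined in Section 3.2". The same section expects that MEPs will not be reliably elicited in some participants, and for them it uses the vertex as target.

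**Assessment threshold (Section 3.2, Neurophysiological Measures).** For assessments, motor threshold is the "minimum TMS intensity required to elicit MEPs of ≥50" μV in at least 5 of 10 trials, measured "at rest (resting motor threshold, RMT) or during slight voluntary contraction (active motor threshold, AMT". Recruitment curves run from 100% to 150% of motor threshold, without saying which of the two.

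**Use of the threshold (Section 1.3).** A fall in tibialis anterior motor threshold is one of several and/or signs of greater corticospinal excitability in the secondary hypothesis. Table 3 lists corticospinal excitability as exploratory, measured by MEP amplitude and latency, and does not list threshold.

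**The concern.** Active versus sham TMS is the only planned difference between the arms, so the intensity rule defines the experimental component. For a participant who cannot contract, two sentences of that rule apply and can give different intensities. Two operators, or the two sites, could each follow the text and deliver different stimulation to similar participants.

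The case is realistic. Eligibility needs AIS C or D and a LEMS above 10 over ten muscle groups scored 0 to 5. A participant with grade 0 in both ankle dorsiflexors still has eight groups, worth up to 8 × 5 = 40 points, from which to qualify. Section 2.5.1 itself foresees contraction failing because of motor impairment.

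On the outcome side, a threshold that may be taken at rest at one visit and during contraction at another does not measure the same thing twice. A participant who regains contraction during the trial could show a lower threshold for that reason alone.

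**Working it through.** **1. Do the two fallbacks overlap?** The possible cases under Section 2.5.1 are:

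- AMT measurable: 80% of AMT at the 200 μV criterion. One rule, no conflict.
- Contraction possible, but AMT not determinable: only the output fallback applies.
- Contraction not possible, RMT measurable: AMT cannot be determined, so the output fallback applies; contraction fails, so the RMT fallback applies too. No order is stated.
- Contraction not possible and no RMT: the RMT sentence cannot be carried out, which in practice leaves the output fallback.

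The conflict has numerical consequences in the third case.

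**2. How far apart are the rules for one participant?** The document gives no threshold values, so RMT (in % of maximum output) is an assumption. If the 80% factor carries over to RMT, which the text does not say:

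ratio = (0.8 × 100) / (0.8 × RMT) = 100 / RMT

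| Assumed RMT (% output) | 80% of RMT | Output fallback | Ratio | Output fallback as % of RMT |
|---|---|---|---|---|
| 40 | 32 | 80 | 2.50 | 200 |
| 50 | 40 | 80 | 2.00 | 160 |
| 60 | 48 | 80 | 1.67 | 133 |
| 70 | 56 | 80 | 1.43 | 114 |
| 80 | 64 | 80 | 1.25 | 100 |
| 90 | 72 | 80 | 1.11 | 89 |
| 100 | 80 | 80 | 1.00 | 80 |

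With the factor carried over, the rules agree only at RMT = 100%. Below RMT = 80%, the output fallback lies above the participant's own resting threshold, whereas 80% of RMT lies below it by construction. If the factor does not carry over and RMT itself is used, the last column is the ratio in percent (200% down to 80%), and the rules agree at RMT = 80%. The silence on the factor is therefore part of the ambiguity.

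**3. The two AMT criteria.** Section 2.5.1 sets the AMT amplitude at 200 μV. Section 3.2 sets 50 μV for both RMT and AMT. Section 3.2 is labelled for assessments, and Section 2.5.1 refers to it only for RMT. Dosing from a measured AMT therefore uses 200 μV. One term still carries two definitions, and a treatment AMT cannot be compared with an assessment AMT.

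**4. What could a change of muscle state do to the threshold outcome?** If RMT is recorded at baseline and AMT at Week 16 with no change in excitability:

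apparent reduction = 1 − AMT/RMT

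For an assumed AMT/RMT of 0.95, 0.90, 0.80 and 0.70, this is 5%, 10%, 20% and 30%. For the arm comparison, with shares p₁ and p₂ switching in the two arms:

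spurious difference = (p₁ − p₂) × (1 − AMT/RMT)

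- 20% versus 10% switching, ratio 0.8: 0.10 × 0.20 = 2% of RMT
- 30% versus 10% switching, ratio 0.8: 0.20 × 0.20 = 4% of RMT
- 10% in each arm: 0

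**5. Is the rest of the iTBS description consistent?** Two seconds at 5 bursts per second, 3 pulses each, gives 30 pulses per train. Then 600 / 30 = 20 trains, and 20 × 2 + 19 × 8 = 192 s, which matches the stated figure of about 190 s. On this check, the pulse pattern is not at fault.

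**The case against.** The strongest reply is that the two fallbacks can be read together. The RMT sentence deals with one named cause, failure to contract, and the output clause could be meant for participants with no measurable threshold at all. That reading is possible and would remove the conflict. It is not written down, however, and the output clause as worded covers every participant without an AMT. The missing factor for RMT would also remain.

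It can also be said that the affected group may be small. LEMS must exceed 10 and participants must be able to attempt the walking tests. This limits the number but does not guarantee contraction in the target muscle, and the protocol gives no expected count.

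Fixing the muscle state across visits could be detail that an article leaves to a fuller document. That has weight, and it is why the outcome point is secondary. It is raised because Section 3.2 states the either/or definition while Section 1.3 counts a threshold reduction as evidence.

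A reader might infer more than the document supports:

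- *That active-arm intensity in general is not reproducible.* Where AMT can be measured, Section 2.5.1 fixes it.
- *That fallback participants receive a stated multiple of what other participants receive.* That compares different people with different thresholds. If no MEP appears even at full output, the threshold lies above 100% of output, and 80% of output is then below 80% of that threshold.
- *That the MEP-present versus MEP-absent subgroup in Section 5.4 is a separate error.* It asks "whether preservation of corticospinal tract conduction is a prerequisite for, or modifier of, treatment response" and is labelled exploratory. Target and intensity rule do differ between the subgroups, but a participant without MEPs cannot have an MEP-confirmed target or a threshold-based dose. Rewording cannot remove that, and active versus sham stays randomised within each subgroup.

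**Conclusion.** The concern holds in a limited form. For active-arm participants who cannot hold a contraction, Section 2.5.1 contradicts itself. If the 80% factor carries over and RMT is 40% to 80% of output (both assumptions), the two rules differ by 2.5 to 1.25 times for the same person. The number of people affected cannot be derived from the document. Because the rule governs the only component that differs between the arms, this is more than missing detail and should be settled before enrolment.

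The double definition of AMT is a lesser, definite inconsistency that does not alter dosing from a measured AMT. The threshold artefact is a possibility: it needs a change of state between visits, and it biases the arm comparison only if such changes are more frequent in one arm. That is plausible if one arm regains more contraction. It would be wrong to infer that it threatens the primary analysis: LEMS is not measured by threshold and is touched only through the intensity delivered. Threshold itself is only an and/or element of the secondary hypothesis.

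**What to change.** - **Section 2.5.1:** the sponsor should reconcile the intensity statements into one ordered rule that places each participant in exactly one branch and says explicitly what factor, if any, applies when RMT is used. Which rule is right is for the sponsor to decide.
- **Sections 2.5.1 and 3.2:** reconcile the 200 μV and 50 μV criteria for AMT, or state that they serve different purposes and give them different names.
- **Section 3.2:** for the threshold outcome and the recruitment curves, fix each participant's muscle state and amplitude criterion at baseline and use the same at Weeks 16 and 20.
- **Section 5.4 (optional):** when interpreting the MEP subgroup, note that target and intensity rule also differ between its two levels.

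The cost is rewording before enrolment. No added visit or procedure, and no change to the sample size, is needed.
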